### **6.3. Interpretation Methods (Statistical Analysis Methods)**

#### **6.3.1. Statistical Analysis**

- This study is a randomized controlled trial of Chuna manual therapy for patients with temporomandibular joint pain, comparing the differences within and between groups based on effectiveness.

#### **6.3.2 General principles of analysis**

- This study analyzes the results of pain intensity scale, functional scale, quality of life, and cost data for patients who meet the inclusion criteria in a randomized controlled trial.
- The primary analysis will use the ITT (Intention-to-Treat) approach, evaluating all subjects who received at least one treatment. Additionally, the PP (Per-Protocol) analysis will be conducted alongside, evaluating only those subjects who completed the clinical study without dropping out. Missing data will be handled primarily through Multiple Imputation, and LOCF (Last Observation Carried Forward) will be used for sensitivity analysis.
- The socio-demographic characteristics and treatment expectancy of the study subjects will be evaluated by group. Continuous variables will be expressed as mean (standard deviation) or median (interquartile range) and compared between the two groups using Student's t-test. Categorical variables will be expressed as frequency (%) and analyzed using the chi-square test or Fisher's exact test.
- The efficacy evaluation variables of this clinical study are the differences in the changes of continuous outcomes (VAS, NRS, MMO, K-BDI-2, JFLS, SF-12, EQ-5D-5L, EQ-VAS) between the two groups from baseline to each time point. ANCOVA (Analysis of Covariance) will be performed with the baseline values of each variable and the covariate factors that show statistical differences between the

treatment groups at baseline as covariates, and the group as a fixed factor. RM ANOVA (Repeated Measures ANOVA) will be conducted to test the differences in trends at each visit.

- To compare the total amount of differences in each outcome within the period (evaluation time point after treatment completion (5 weeks)) and the entire study period (6 months), the areas under the curve (AUC) at each time point after randomization will be calculated and compared using Student's t-test.
- The proportion of patients whose NRS and VAS, indicators of temporomandibular joint pain, fall to less than half of the baseline will be compared and analyzed by time point. Kaplan–Meier survival analysis will be used to measure the time until the recovery of temporomandibular joint pain to less than half after randomization, and the curves will be compared using the log-rank test. A Cox model will be used to calculate the hazard ratio to compare the rate at which temporomandibular joint pain recovers to less than half, and it will also check if the recovery rate differs by subgroup.
- The significance level for all analyses is set at 0.05. All statistical analyses will be performed using the SAS version 9.1.3 statistical package (SAS Institute, Cary, NC, USA), with significance determined at  $p < 0.05$ .

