**Timetable**

| Time point                                                                                  | Study period |                      |                  |        |        |        |                 |         |         |
|---------------------------------------------------------------------------------------------|--------------|----------------------|------------------|--------|--------|--------|-----------------|---------|---------|
|                                                                                             | Enrollment   | Allocation           | Active Treatment |        |        |        | post-allocation |         |         |
|                                                                                             | Week -1      | Week 0
(Baseline) | Week 1           | Week 2 | Week 3 | Week 4 | Week 5          | Month 3 | Month 6 |
| Visit window                                                                         |              |                      | ±3               | ±3     | ±3     | ±3     | ±3              | ±7      | ±7      |
| Eligibility screening                                                                       | ○            |                      |                  |        |        |        |                 |         |         |
| Written Informed consent                                                                    | ○            |                      |                  |        |        |        |                 |         |         |
| Vital signs                                                                                 | ○            |                      | ○                |        |        |        | ○               |         |         |
| Sociodemographic characteristics,
medical history
(e.g. TMJ pain, medication history) | ○            |                      |                  |        |        |        |                 |         |         |
| RDC/TMD test & analysis                                                                     | ○            |                      |                  |        |        |        |                 |         |         |
| Randomized allocation                                                                       |              | ○                    |                  |        |        |        |                 |         |         |

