### 3.4. Discontinuation and Withdrawal Criteria

Patients have the right to voluntarily withdraw from participating in the clinical study at any time, regardless of the reason. Additionally, the investigator has the authority to discontinue a patient's participation in the study.

Reasons for withdrawal from the clinical study may include, but are not limited to, the following:

- Withdrawal of consent by the study subject
- Medical conditions deemed to jeopardize the safety of the patient if the study continues
- When discontinuation of participation is in the best interest of the patient
- Non-compliance with clinical study regulations by the study subject

Efforts will be made to obtain information on patients who discontinue the clinical study, and the reasons for discontinuation of treatment or observation will be recorded. For study subjects whose participation is discontinued, follow-up may continue with patient consent. However, in the event of withdrawal of consent, follow-up will not be conducted, and patients who discontinue participation in the clinical study will not be replaced.

At any time during the clinical study, if a serious adverse event or an adverse reaction deemed harmful to the

study subject is observed, and if subsequent evaluation of the course and causality of the adverse event with the treatment determines that continuation of treatment is harmful to the study subject, the investigator will permanently discontinue the treatment for the patient in this clinical study.

- Study subjects who discontinue before starting treatment are considered screening failures. Unless medically necessary, all required assessments at the time of discontinuation (screening failures) do not have to be completed.
- Subjects who withdraw early due to adverse events may receive appropriate treatment for the adverse events if necessary. In the case of early withdrawal due to adverse events, the investigator or an investigator designee must continuously evaluate the study subject until the adverse event resolves or is deemed permanent.

Other reasons for discontinuation of the clinical study by the investigator include:

- If a disease that could affect the outcome of the study is discovered in the study subject that was not detected in pre-study screening.
- If there are issues performing medical procedures for temporomandibular joint disease in the study subject.

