#### 5.2.2. Allocation concealment and blinding

After providing patients with a thorough explanation of the clinical study, those who meet the inclusion and exclusion criteria and sign the written consent form will be assigned to groups using opaque, sealed envelopes. Since it is not feasible to blind the practitioners and participants in this study, only the assessors will be blinded. Assessor, who do not participate in the procedures and are blinded to group assignments, will conduct assessments in a separate area after the procedures are completed. These evaluations will be performed by clinical research coordinator or residents.

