### **15.2. Deviation from the Clinical Study Protocol**

Investigators and staff must fully understand and strictly adhere to the protocol to prevent violations. To comply with the visit schedule, the staff must take appropriate actions, such as providing written notifications or conducting telephone monitoring for the next visit time. In case of unavoidable protocol violations, the following procedures will apply:

Serious Protocol Violations: For significant violations such as subject withdrawal/drop-out criteria, subject inclusion/exclusion criteria violations, failure to obtain consent, or mid-study drop-out criteria, subjects may be dropped from the study after consultation with the investigator.

Minor Violations: Minor violations must be accurately recorded along with the reasons and extent of the delay, and their impact on the clinical study will be considered during the result analysis.

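### The primary analysis is called ITT but omits randomised subjects who receive no treatment, and no analysis of all randomised subjects is planned

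*Protocol*

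**What the plan says.** Protocol 6.3.2 sets the primary analysis: "The primary analysis will use the ITT (Intention-to-Treat) approach, evaluating all subjects who received at least one treatment". The closing part of the protocol, Statistical Analysis Methods 1.1, repeats this. The only other set is per-protocol, "evaluating only those subjects who completed the clinical study without dropping out". Missing data are to be multiply imputed, with LOCF as a sensitivity analysis.

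Section 3.4 adds a rule on early leavers: "Study subjects who discontinue before starting treatment are considered screening failures". Unless there is a medical need, "all required assessments at the time of discontinuation (screening failures) do not have to be completed". It also says that "patients who discontinue participation in the clinical study will not be replaced".

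The Timetable marks "Randomized allocation" at Week 0, and treatment begins in Week 1. Under 5.2.1 each site receives the allocation and then treats accordingly. On blinding, 5.2.2 says: "Since it is not feasible to blind the practitioners and participants in this study, only the assessors will be blinded".

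**The concern.** Intention-to-treat means that everyone randomised is analysed in the arm assigned. Requiring at least one treatment is often harmless when nobody knows the arm before the first dose, because starting treatment then cannot depend on the allocation. That protection is absent here: participants and practitioners know the arm before the first session, and the two treatments are visibly different. A subject who declines to start may do so because of the allocation.

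If that happens more in one arm than in the other, or among different kinds of patient, the arms compared are no longer the arms that were randomised. Section 3.4 adds two problems. The label of screening failure could keep such a subject out of the dropout count. Waiving the assessments means that the outcome may never be collected, and no later analysis plan could recover it.

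**Working it through.** **Whether the exclusion can occur**

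1. Order of events: allocation at Week 0, result sent to the site, then treatment from Week 1 (Timetable; 5.2.1). There is an interval between allocation and first treatment.
2. Length of that interval: the Timetable notes put visit 2, the first treatment visit, 0 to 3 days after screening. Allocation falls inside that window, so the interval is at most 3 days.
3. Knowledge of the arm: only assessors are blinded (5.2.2).
4. Analysis set: at least one treatment is required (6.3.2 and 1.1), so a subject lost in the interval is excluded.
5. Data: section 3.4 does not exempt randomised subjects from the screening-failure rule or from the waiver of assessments.
6. Back-up: the completers' set also excludes such a subject. No stated analysis includes all randomised subjects.

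**How large the effect could be**

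The plan gives no figure for untreated randomised subjects, so there is none to reproduce. It supplies 40 subjects per arm, an assumed effect of 0.7 SD and an assumed baseline-to-endpoint correlation of 0.3 (3.5).

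Let k of the 40 in one arm be excluded, and let their mean outcome differ from that of the retained subjects by D. Then

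bias in that arm's mean = (k/40) × D.

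In millimetres of VAS, with k from 2 to 6 and D from 10 to 20 mm (both assumed):

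- 2/40 × 10 = 0.5 mm
- 4/40 × 20 = 2.0 mm
- 6/40 × 20 = 3.0 mm

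In SD units, with D of 0.5 or 1 SD (assumed), the last column gives the two-sided rejection rate at nominal 0.05 when there is no true difference among all randomised subjects. It uses a normal approximation with residual SD √(1 − 0.3²) = √0.91, standard error √0.91 × √(1/40 + 1/(40 − k)), shift = bias/standard error, and rate = Φ(shift − 1.96) + Φ(−shift − 1.96).

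| k of 40 | D (SD) | Bias (SD) | Share of 0.7 SD | Rejection rate |
|---|---|---|---|---|
| 1 | 0.5 | 0.013 | 1.8% | 0.0504 |
| 1 | 1.0 | 0.025 | 3.6% | 0.0516 |
| 2 | 0.5 | 0.025 | 3.6% | 0.0515 |
| 2 | 1.0 | 0.050 | 7.1% | 0.0562 |
| 4 | 0.5 | 0.050 | 7.1% | 0.0560 |
| 4 | 1.0 | 0.100 | 14.3% | 0.0742 |
| 6 | 0.5 | 0.075 | 10.7% | 0.0631 |
| 6 | 1.0 | 0.150 | 21.4% | 0.1035 |

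The documents give no SD in millimetres, so the two scales are separate sets of assumptions. The direction of the bias is not determined either.

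**What imputation can recover**

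VAS is first scheduled at the first treatment visit (Timetable; 6.1), while the NRS is taken at screening (Timetable; 6.2). A subject who is never treated therefore has neither the Week 5 VAS nor the baseline VAS that the ANCOVA needs. If screening NRS predicts Week 5 VAS no better than the plan assumes for baseline VAS, it explains 0.3² = 0.09 of the variance.

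**The case against.** The best defence is that little is exposed. With visit 2 on the day of screening or at most 3 days later, few subjects can be randomised and then lost before a first session. No rate is given, and every size above is assumed. This stands, and it points to the lower end of the range.

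Second, section 3.4 never mentions randomised subjects. The Summary of Protocol uses the term study subjects for people who have consented but are not yet assessed for eligibility, so the sentence may describe ordinary failures before randomisation. A reader might infer that the plan intends to relabel randomised subjects. The text does not say that; it only fails to exclude it. The restriction in 6.3.2 applies in either case.

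Third, imputing from screening data is weak. That also stands, and it is why the remedy must include an attempt to collect the outcome.

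Three stronger readings are tempting but not supported:

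- *Section 15.2 removes violators from the primary set.* It says that "subjects may be dropped from the study after consultation with the investigator". That concerns participation. Under 6.3.2 anyone treated once is still evaluated, and 3.4 allows continued follow-up with consent.
- *The per-protocol set keeps users of prohibited treatment.* Section 3.4 lists non-compliance, and outside treatment that could affect the outcome, as grounds for discontinuation. Subjects discontinued on those grounds are not completers.
- *The per-protocol set loses adherent patients who miss only Month 6.* The protocol does not equate one missed visit with dropping out, and 5.1 allows the follow-up survey by telephone or questionnaire.

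**Conclusion.** The point holds for the primary analysis set. The protocol names it ITT, defines a modified set, and plans no analysis of all randomised subjects. The open-label design and the order of allocation and treatment mean that the exclusion can depend on the arm. The literal wording of 3.4 means that the missing outcomes need not be sought.

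This establishes a route for bias, not that bias will occur. A reader might suppose that patients come for Chuna and will leave when given usual care, but the documents do not show this. With 2 to 6 of 40 lost in one arm and a difference of 10 to 20 mm, both assumed, the bias is 0.5 to 3.0 mm on a 100 mm scale. The short window makes the lower end likelier. The correction should be made, because it is cheap and affects the primary endpoint. The size does not support calling it a critical flaw.

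**What to change.** - In 6.3.2 and Statistical Analysis Methods 1.1, define the primary set as all randomised subjects, analysed in the arm assigned.
- In 3.4, limit screening failure, and the waiver of assessments that goes with it, to subjects not yet randomised.
- Seek the Week 5 VAS from randomised but untreated subjects who have not withdrawn consent. Section 3.4 already allows follow-up with consent and bars it after withdrawal of consent.
- Where the Week 5 VAS cannot be obtained, multiply impute it using screening NRS and demographics, since no VAS is scheduled before randomisation. The missing baseline VAS needs the same treatment.
- Keep the treated-at-least-once set as a sensitivity analysis, labelled modified ITT.
- Report by arm how many randomised subjects were never treated.

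The cost is wording in three places, contact at Week 5 with what are probably few subjects, and a few imputed records with weak predictors. Imputation alone would not remove a difference tied to the allocation itself, so the attempt to collect the outcome matters more.

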| EQ-5D-5L                                                                                    |              |                      | ○                |        |        |        | ○               | ○       | ○       |
| EQ-VAS                                                                                      |              |                      | ○                |        |        |        | ○               | ○       | ○       |
| SF-12                                                                                       |              |                      | ○                |        |        |        | ○               | ○       | ○       |
| Economic evaluation-Medical costs                                                           |              |                      | ○                |        |        |        | ○               | ○       | ○       |
| Economic evaluation-Time costs                                                              |              |                      |                  | ○      |        |        |                 |         |         |
| Economic evaluation-Productivity loss                                                       |              |                      | ○                | ○      | ○      | ○      | ○               | ○       | ○       |
| Adverse events                                                                              |              |                      | ← every visit →  |        |        |        | ○               | ○       | ○       |

\* NRS, VAS K-BDI-2, JFLS, TMJ Range of Motion, PGIC, EQ-5D-5L, EQ-VAS, SF-12, measurements for economic evaluation are conducted during the first visit of the relevant week.

\* During the clinical period, visits scheduled for Week 1 to Week 5 are allowed within ± 3 days of the scheduled visit date, and visits scheduled for 3 months and 6 months after the first visit (visit 2) of Week 1 are allowed within ± 7 days of the scheduled visit date.

\* Subjects selected during the screening visit will begin visit 2 on the same day or within 3 days.

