### **5.2. Random allocation and blinding**

#### **5.2.1. Random allocation**

When subjects who have voluntarily signed the informed consent form are reviewed and determined to meet the inclusion and exclusion criteria, and thus are deemed suitable for the clinical study, they will be assigned to one

of two groups using a block randomization method. This method will be implemented by a statistician using nQuery Advisor 7.0 (or SAS 9.0 or SPSS 21.0), with an equal number of patients (40 each) allocated to both groups. The block size will remain undisclosed to the personnel conducting patient recruitment and group allocation.

Random assignment will occur based on patient registration at each of the five institutions, without stratification by institution. Patient recruitment will follow a competitive enrollment process at each hospital and will continue until the total number of patients is achieved. Participants will be assigned an identification code (Randomized Number) in the order of recruitment according to the random allocation details. The results of the central randomization will be communicated to each institution conducting the clinical study, and treatment will proceed accordingly in each group.

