### 1.1 General principles of analysis

- This study analyzes the results of pain intensity scale, functional scale, quality of life, and cost data for patients who meet the inclusion criteria in a randomized controlled trial.
- The primary analysis will use the ITT (Intention-to-Treat) approach, evaluating all subjects who received at least one treatment. Additionally, the PP (Per-Protocol) analysis will be conducted alongside, evaluating only those subjects who completed the clinical study without dropping out. Missing data will be handled primarily through Multiple Imputation, and LOCF (Last Observation Carried Forward) will be used for sensitivity analysis.
- The socio-demographic characteristics and treatment expectancy of the study subjects will be evaluated by group. Continuous variables will be expressed as mean (standard deviation) or median (interquartile range) and compared between the two groups using Student's t-test. Categorical variables will be expressed as frequency (%) and analyzed using the chi-square test or Fisher's exact test.
- The efficacy evaluation variables of this clinical study are the differences in the changes of continuous outcomes (VAS, NRS, MMO, K-BDI-2, JFLS, SF-12, EQ-5D-5L, EQ-VAS) between the two groups from baseline to each time point. ANCOVA (Analysis of Covariance) will be performed with the baseline values of each variable and the covariate factors that show statistical differences between the treatment groups at baseline as covariates, and the group as a fixed factor. RM ANOVA (Repeated Measures ANOVA) will be conducted to test the differences in trends at each visit.
- To compare the total amount of differences in each outcome within the period (evaluation time point after treatment completion (5 weeks)) and the entire study period (6 months), the areas under the curve (AUC) at each time point after randomization will be calculated and compared using Student's t-test.

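### The primary analysis is called ITT but is limited to subjects who had at least one treatment session, and no analysis of all randomised subjects is planned

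*Protocol*

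**What the plan says.** **Analysis set.** Section 6.3.2 names the primary analysis ITT and describes it as "evaluating all subjects who received at least one treatment". Section 1.1 of the Statistical Analysis Methods has the same wording: "The primary analysis will use the ITT (Intention-to-Treat) approach, evaluating all subjects who received at least one treatment". The one other set described is per-protocol, meaning subjects who completed without dropping out. Multiple imputation is the main method for missing data, with LOCF as sensitivity analysis.

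**Order of events.** The Timetable places allocation at Week 0 and treatment from Week 1, with the footnote "Subjects selected during the screening visit will begin visit 2 on the same day or within 3 days". Section 5.2.1 says "The results of the central randomization will be communicated to each institution conducting the clinical study, and treatment will proceed accordingly in each group".

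**Blinding.** Section 5.2.2: "Since it is not feasible to blind the practitioners and participants in this study, only the assessors will be blinded".

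**Departure before treatment.** Section 3.4: "Study subjects who discontinue before starting treatment are considered screening failures". It adds that, unless there is a medical need, "all required assessments at the time of discontinuation (screening failures) do not have to be completed". The same section says that "patients who discontinue participation in the clinical study will not be replaced" and allows follow-up of discontinued subjects who agree to it, but not of those who withdraw consent.

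**The concern.** Having a first session is an event after randomisation. A set conditioned on it is protected by randomisation only if starting treatment is unrelated to the arm. Here the participant and the practitioner both know the arm before the first session. Section 11 recruits by press releases and posters for a trial whose title names Chuna, and the control is one physical modality. Someone hoping for Chuna who is allocated to the control could plausibly decide not to start. That person would drop out of the primary comparison, and the text plans no wider analysis that would show the effect of the loss.

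Section 3.4 adds a difficulty. Its sentence on screening failures makes no exception for subjects already allocated. On that reading, an arm-related loss would be reported as a screening failure and would not appear in the flow of randomised subjects.

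Because the protocol fixes the set in two places under the name ITT, readers of the primary result would take it for something it is not.

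**Working it through.** **1. What each set contains.**

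- All randomised: the 80 subjects allocated, 40 per arm (Section 5.2.1). No analysis of this set is described.
- Primary set, named ITT: those allocated less those who had no session.
- Per-protocol: completers only, so narrower again.

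**2. Does the planned imputation restore the missing subjects?** No. It fills gaps within a set that already omits them. VAS is first taken at the first treatment visit (Section 6.1 and Timetable), so an allocated but untreated subject may have no VAS at all. The NRS is taken at screening (Section 6.2 and Timetable), so one pain score should exist.

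**3. Length of the exposed interval.** The Week 0 and Week 1 columns suggest a week. The Timetable footnote puts the first treatment visit on the screening day or within 3 days. Allocation falls inside that window, so the interval is at most about 3 days and may be nil.

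**4. The plan's own benchmark.** Section 3.5 assumes an effect of 0.7 SD, two-sided alpha 0.05 and power 80%. The two-sample t-test gives 33.02, so 34 per arm and 68 in total, as stated. The ANCOVA factor gives (1 − 0.3²) × 68 = 61.88, so 62, also as stated. These figures do not test the present point. They supply the 0.7 SD against which a bias can be judged.

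**5. Size of a possible bias.** The documents give no rate of departure before treatment, so the inputs are assumptions: k of 40 leave one arm and none leave the other, and the leavers' Week 5 VAS would have differed from that of the remaining subjects by g SD. The arm mean then shifts by

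bias = (k/40) × g.

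The standard error of the difference with 40 per arm, in SD units without baseline adjustment, is √(2/40) = 0.22.

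| k | g | Bias (SD) | Share of 0.7 SD | Share of 0.22 SE | Two-sided type I error |
|---|---|---|---|---|---|
| 2 | 0.5 | 0.025 | 4% | 11% | 0.052 |
| 2 | 1.0 | 0.05 | 7% | 22% | 0.056 |
| 4 | 0.5 | 0.05 | 7% | 22% | 0.056 |
| 4 | 1.0 | 0.10 | 14% | 45% | 0.074 |

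The type I error assumes no true effect and uses the ANCOVA standard error √(1 − 0.3²) × √(1/(40 − k) + 1/40). For k = 4 and g = 1.0 this is 0.954 × 0.230 = 0.219. The shift is 0.10/0.219 = 0.456 standard errors, and P(Z > 1.96 − 0.456) + P(Z < −1.96 − 0.456) = 0.066 + 0.008 = 0.074.

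With k = 0 the bias is zero. At k = 6, which is 15% of one arm, it would be 0.075 to 0.15 SD.

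**The case against.** The strongest reply is that the exposure is small. The interval is at most about 3 days, and k = 4 means 10% of one arm leaving in that time with none leaving the other. The assumed bias is at most 45% of one standard error. This stands, and it limits how serious the point is. It does not make the definition right: the set is still not what its name says, and the arm is known before the first session.

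Three stronger readings may tempt a reader, and the documents do not support them.

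- *That Section 3.4 expressly turns randomised subjects into screening failures.* The sentence does not mention randomisation. It may mean only people who leave between consent and allocation. Its wording is unrestricted and can be read to cover allocated subjects, but that is one reading. The waiver of assessments is also limited to those due at discontinuation and has an exception for medical need.
- *That the protocol contradicts itself on replacement.* Recruitment runs until the target is met, but nothing says that an allocated, untreated subject stops counting towards the 80, and no rule adds or reuses randomisation numbers. Such a subject could be replaced, contrary to Section 3.4's own statement, only if that section's screening-failure sentence covers allocated subjects.
- *That there is a week between allocation and treatment.* The Timetable footnote rules this out.

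A further objection concerns the remedy. Imputing these subjects under missing at random, with the screening NRS as the only pain score, would largely reproduce the treated-set result. This is correct, and it is why the remedy must start with collecting the outcome.

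**Conclusion.** The point holds as a mislabelled and too narrow primary set. Sections 6.3.2 and 1.1 define a treated-subjects set, call it ITT, and plan no analysis of all randomised subjects. With open allocation before the first session, exclusions can depend on the arm.

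The likely size is small: 0.025 to 0.10 SD if 2 to 4 of 40 leave one arm only and differ by 0.5 to 1.0 SD, and nothing if nobody leaves. Both the count and the gap are assumptions, and the direction is unknown. It would go too far to infer that the primary result will be materially biased. Section 3.4's sentence on screening failures is ambiguous and needs clarifying. This should be fixed, but it does not by itself undermine the trial.

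**What to change.** - **Sections 6.3.2 and 1.1:** define the primary set as every randomised subject, analysed in the arm assigned. Keep the present set as a sensitivity analysis under an accurate name, such as treated subjects.
- **Section 3.4:** limit the term screening failure to departures before allocation, and state that each allocated subject counts among the 80.
- **Outcome collection:** seek the Week 5 VAS from allocated but untreated subjects through the follow-up that Section 3.4 already permits with their agreement. It cannot be obtained from those who withdraw consent.
- **Imputation:** use the planned multiple imputation, with the screening NRS as an auxiliary variable, only for VAS values (baseline or Week 5) that remain missing. State that it relies on missing at random.

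The cost is wording in three sections, a Week 5 contact for what is likely to be a handful of subjects, and a few more imputed values. The planned sample size does not change.
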